### Selection Criteria

Inclusion criteria include 18 years of age or older; diagnosis of affective or nonaffective psychosis or related disorder; followed and treated by a clinician at one of the services mentioned earlier; considered symptomatically stable and capable of using the digital platforms and participating in intervention groups, as judged by their primary clinicians; access to a private space to ensure group confidentiality; and provision of emergency contact and consent to allow researchers to contact their clinician or emergency services in the event of an emergency during study procedures. Most criteria are present for the safety of the group and participants. Exclusion criteria include intellectual disability, hospitalization at the time of recruitment, inability to speak or read English or French, and high suicide risk as per evaluation. We will recruit 4-6 mental health practitioners per site who will complete training on the E-Cog training platform to deliver the 2 cognitive health interventions. Practitioners will be eligible if they have a background in psychology, social work, nursing, or any other health-related training.

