**Objective:**

The iCogCA study aims to address this gap by implementing digital ABCR and MCT through a national Canadian collaborative effort using digital psychological interventions to enhance cognitive health in SSDs.

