**Methods:**

The study involves 5 Canadian sites, with mental health care practitioners trained digitally through the E-Cog platform, which was developed by our research group. Over 2.5 years, participants with SSDs will undergo pre- and postintervention assessments for clinical symptoms, cognition, and functioning. Each site will run groups annually for both ABCR and MCT, totaling ~390 participants. A nonrandomized concurrent controlled design will assess effectiveness design, in which one intervention (eg, ABCR) acts as the active control for the other (eg, MCT) and vice versa, comparing cognitive and clinical outcomes between the interventions using generalized linear mixed effect modeling. Implementation strategy evaluation will consider the digital platform’s efficacy for mental health care practitioners’ training, contextual factors influencing implementation, and sustainability, using descriptive statistics for quantitative data and thematic analysis for qualitative data.

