### Study Setting

This study takes place across 5 sites providing care to those with psychotic disorders across Canada. These sites include the Centre intégré universitaire de santé et de services sociaux (CIUSSS) de l’Ouest-de l’Ile de Montréal, Royal Ottawa Health Care Group, Kingston Health Sciences Centre, Ontario Shores Centre for Mental Health Sciences in Toronto, and Vancouver Coastal Health. We will recruit 390 service users across the 5 sites.

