### Cognitive Health Interventions

Interventions will be delivered through a secure videoconference platform. Network-connected tablets will be provided as necessary for the trial duration. ABCR [27,64] sessions consist of computer-based cognitive training activities (Brain Training Pro; 60%), teaching of problem-solving strategies (20%), and transfer activities (20%). Transfer activities include discussing and role-playing how cognitive skills are applied in everyday life and teaching potential strategies for overcoming cognitive challenges. ABCR targets include processing speed, attention, memory, executive functions, and social cognition, which are all commonly impaired in psychosis [12]. ABCR will be delivered in 16 sessions lasting 1.5 hours each over an 8-week period. MCT targets cognitive biases and errors in judgment underlying delusions using the theoretical foundations of cognitive behavioral therapy [65]. Sessions consist of discussions and activities aimed at increasing participants’ awareness of distortions and expanding their current problem-solving strategies. MCT will be delivered in 12 sessions lasting 45-60 minutes each over 6 weeks.

Both interventions will be offered at all sites. Depending on the site, interventions will either be offered concurrently or in sequence. Intervention group allocation follows a personalized, participant-centered approach. Potential participants will meet individually with the research coordinator at their site, who will provide a comprehensive overview of both interventions. Together, they will collaboratively determine which intervention best aligns with the participant’s personal goals and preferences. To maximize participant benefit and engagement, individuals will have the opportunity to complete the alternative intervention after finishing their initial chosen intervention. This flexible approach ensures that participants can potentially benefit from both interventions.

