#### Data Analysis

Data related to the analysis of objective 1, focusing on clinical effectiveness, will be compared between both interventions. Primary and secondary outcomes will be compared between the 2 interventions, using one as the active control for the other. First, propensity score matching will be used to identify a subset of participants who will comprise the active control group that is equivalent to the intervention group on background variables (sociodemographic variables, illness duration, medication dosage, length and nature of prior treatment as well as subjective reports of cognitive capacity and cognitive biases). Then, Z-standardized outcome data will be compared between the groups with generalized linear mixed effect modeling techniques using R software. Factors of interest will include fixed time (pre, post, and follow-up), fixed treatment (ABCR and MCT), fixed time and treatment interaction (time*treatment), random site (CIUSSS de l’Ouest-de l’Ile de Montréal, the Royal’s Institute in Ottawa, Kingston Health Sciences Centre, Ontario Shores Centre for Mental Health Sciences in Toronto, and Vancouver Coastal Health), random intercepts (participants’ ID), and random slopes (participant*time). Age, illness duration, medication dosage, length, and nature of prior psychological treatment will also be included as fixed covariates. This procedure will be done twice, with the active control group subset using propensity score matching. This approach ensures that participants are not counted twice and is an integral part of the propensity score matching procedure. Statistically, performing the procedure twice helps to validate the robustness of the matching process without introducing bias, as each participant is only included once in each comparison. Specifically, the procedure will be as follows: (1) ABCR as the intervention and MCT as the active control and (2) MCT as the intervention and ABCR as the active control. Missing data pattern will be assessed for whether it is missing completely at random, missing at random, or not at random [73]. If data are missing at random, multiple imputation will be applied [74]; if data are missing not at random, then the robustness of the primary analyses will be evaluated through sensitivity analyses.

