### Principal Findings and Comparison to Prior Work

The objectives of this study are 2-fold, focusing on both service users and mental health care providers. The first objective aims to assess the effectiveness of digital cognitive health interventions in enhancing accessibility and engagement for individuals with SSD. If proven effective, these interventions may provide an evidence-based framework for other service providers providing care for individuals with psychotic disorders and could be adapted for other populations receiving mental health services where these interventions show similar efficacy (eg, mood disorders) [78,79]. Objective 2 aims to identify facilitators and barriers to digital delivery and a digital training platform for clinicians. We anticipate that this study will introduce and validate our platform to train and supervise mental health care practitioners to deliver these interventions, which will then be made accessible to the broader mental health community. Further, these findings will furnish crucial information for the implementation of digital health technologies to improve access to psychosocial therapies for optimized care. These findings will be used to guide the implementation of similar projects across Canada. Notably, New York State has already fully integrated CR into its psychiatric care systems [80], and parallel efforts are underway in Australia [81] and the United Kingdom [82]. Collaborating with a National Steering and Implementation Committee, we will test our set of tools based on the CFIR and make them accessible to the mental health community. Site-specific implementation committees, which include patient partners, will assist with the local implementation of our cognitive health interventions.

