### Conclusions

In summary, this project aims to address pressing clinical needs related to cognitive impairments and biases in SSDs. By leveraging digital technologies, it aims to facilitate the adoption of evidence-based interventions within clinical settings, support future implementation of similar initiatives, and validate an adaptable platform designed for widespread use.

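### Eligibility is wider than the stated schizophrenia spectrum population, and diagnosis, a potential confounder in a preference-allocated comparison, is not in the listed matching variables or covariates

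*Protocol article*

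**What the plan says.** **Who is enrolled.** The Selection Criteria section requires a "diagnosis of affective or nonaffective psychosis or related disorder". The Study Setting section matches that breadth: "This study takes place across 5 sites providing care to those with psychotic disorders across Canada".

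**Who the study is said to be about.** The abstract's objective speaks of "using digital psychological interventions to enhance cognitive health in SSDs". Its methods paragraph says that "participants with SSDs will undergo pre- and postintervention assessments for clinical symptoms, cognition, and functioning". The Discussion overview puts the aim in terms of people with SSD, and the closing Conclusions say that "this project aims to address pressing clinical needs related to cognitive impairments and biases in SSDs".

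**How people reach an intervention.** Allocation is not randomized. Under Cognitive Health Interventions, coordinator and participant "collaboratively determine which intervention best aligns with the participant’s personal goals and preferences".

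**What is adjusted for.** The Data Analysis section lists the matching variables as sociodemographics, illness duration, medication dosage, the duration and type of earlier treatment, and self-reported cognition and biases. For the mixed model it adds: "Age, illness duration, medication dosage, length, and nature of prior psychological treatment will also be included as fixed covariates". Diagnosis is in neither list. The Measures section gives much the same matching list, introduced as examples, again without diagnosis. The only subgroup analyses named in the Power section are by sex and gender.

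**The concern.** The first issue is whom the answer describes. If people with affective psychosis are enrolled and analysed together with the rest, a conclusion worded for SSDs rests in part on participants who may not have one. No analysis named in the article would separate them.

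The second is comparability. Each intervention serves as the control for the other, and participants select between them by goals and preferences. The comparison is then only as good as the adjustment set. Diagnostic group is a basic clinical descriptor that could bear on what a participant wants from treatment and on how much he or she changes. The limitations paragraph relies on statistical control of measurable background characteristics to answer concerns about nonrandomized groups. Diagnosis is such a characteristic and has to be determined before entry, yet the article does not list it.

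**Working it through.** The plan gives no figure on this point to reproduce. The check has two parts.

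**1. Text comparison**

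| Place in the article | Population named |
|---|---|
| Abstract, objective and methods | SSDs |
| Objectives section, first objective | none named |
| Study Setting | psychotic disorders |
| Selection Criteria | affective or nonaffective psychosis, or related |
| Discussion, overview | SSD |
| Discussion, principal findings | both SSD and psychotic disorders; mood disorders given as an example of another population |
| Conclusions | SSDs |

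The operative criterion is the broad one. The narrower label is used where the aim and the conclusions are stated.

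**2. Possible size of bias**

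Let p1 and p2 be the shares with affective psychosis in the two compared groups, and g the difference in mean change between affective and nonaffective participants, in SD. Mean change in group k is then its own level plus pk × g. The between-group contrast in change, which the treatment-by-time interaction estimates, is shifted by

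bias = (p1 − p2) × g.

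The documents give neither p1 − p2 nor g, so both are assumptions. The anticipated primary effects, g=0.27 for MCT and d=0.50 for cognitive remediation, come from the Power section.

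Working case, g = 0.3 SD:
- 10-point imbalance: 0.10 × 0.3 = 0.03 SD; 0.03/0.27 = 11%; 0.03/0.50 = 6%.
- 20-point imbalance: 0.20 × 0.3 = 0.06 SD; 0.06/0.27 = 22%; 0.06/0.50 = 12%.

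For the effect on type I error, take the 300 participants of the Power section split equally, 150 per arm (also an assumption), with outcome SD 1. The standard error is √(2/150) = 0.1155. The two-sided 5% rejection rate when there is no true difference is Φ(bias/0.1155 − 1.96) + Φ(−bias/0.1155 − 1.96).

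| Imbalance | g (SD) | Bias (SD) | % of 0.27 | % of 0.50 | False-positive rate |
|---|---|---|---|---|---|
| 10 points | 0.2 | 0.02 | 7% | 4% | 5.3% |
| 10 points | 0.3 | 0.03 | 11% | 6% | 5.8% |
| 20 points | 0.3 | 0.06 | 22% | 12% | 8.1% |
| 20 points | 0.5 | 0.10 | 37% | 20% | 13.9% |
| 40 points | 0.5 | 0.20 | 74% | 40% | 41% |

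The last row needs a very large imbalance and a large difference in change together. Nothing in the documents supports either, and it is shown only to mark the end of the range. All rows are gross figures, with nothing absorbed by the other adjustment variables.

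**The case against.** A reader might infer that diagnosis is a confounder left uncontrolled and that it will bias the contrast after matching. The documents do not support that. Confounding of the treatment-by-time effect needs a link from diagnosis to choice of intervention and another from diagnosis to change, and neither is shown. It is tempting to argue that MCT addresses reasoning behind delusions and so draws particular diagnoses. But every participant must have a psychotic or related diagnosis and be clinically stable, and the article does not say that delusions or interest in MCT separate affective from nonaffective psychosis.

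Several features also limit the damage. Self-reported cognition and biases, the likeliest reasons for preferring one intervention, are in the propensity score. Illness duration, medication dosage and treatment history carry some diagnostic information. The pre-to-post contrast and participant random intercepts remove stable differences in level between diagnoses, which leaves only differences in change.

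The Measures section offers its matching list as examples, and a full propensity specification may sit in an analysis plan that is not shown. On population, the first objective names no diagnosis, and broad entry suits a trial meant to resemble routine care.

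Most of this stands, and it lowers the weight of the point. It does not remove it. The Data Analysis section sets out a specific matching list and specific covariates, both without diagnosis, and none of the listed variables replaces it. Broad entry is not the problem; the narrower label on the aim and conclusions is.

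**Conclusion.** The point holds as a mismatch between enrolled and stated population, together with a potential confounder missing from the listed adjustment set. Under the assumed 10- to 20-point imbalance and 0.3 SD difference in change, bias would be about 0.03 to 0.06 SD before absorption: modest against d=0.50, less so against g=0.27. Its true size and direction are unknown, and it is zero if diagnosis is unrelated either to choice or to change.

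A reader might also infer that an SSD-only analysis is obligatory. It is not: consistent wording for the broader population would resolve the mismatch equally well. The change is still worth making, because the comparison depends on measured covariates and the variable concerned is part of eligibility.

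**What to change.** 1. Add diagnostic group (affective versus nonaffective) to the propensity score variables and to the fixed covariates in the Data Analysis section.
2. Resolve the population in one of two ways: describe it as psychotic disorders in the abstract, the Discussion and the Conclusions, or keep SSD-specific conclusions and support them with a pre-specified sensitivity analysis restricted to participants with an SSD.

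Eligibility need not change. The costs are one more matching variable, which may make matches slightly harder to find; the need to record diagnostic group in the same way at all 5 sites, since the criterion asks only for a broad diagnosis and Table 1 lists no diagnostic measure; and lower precision in any restricted analysis. With 114 of 390 participants recruited as of winter 2024, uniform recording can be set up for later entrants, but the diagnostic group of those already enrolled may have to be retrieved from site records.

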### Recruitment

Recruitment for this study uses a multimodal communication strategy designed to effectively reach potential participants. This strategy includes displaying informational flyers on hospital television screens, distributing email newsletters to health care employees, and presenting intervention details to case managers to facilitate referrals. Additionally, recruitment materials will be posted in clinic waiting rooms. n example of the recruitment pamphlet is provided in Multimedia Appendix 1. Health care team members can refer eligible participants or obtain consent for the research team to make direct contact. Participants are permitted to be engaged in other psychological or psychosocial interventions while participating in our study. Data on whether they are currently receiving other interventions will be collected.

### Ethical Considerations

This study has been approved by the respective research ethics boards (REBs) of the 5 mental health sites and their partner institutions. The study will be conducted in Montreal (CIUSSS de l’Ouest-de l’Ile de Montréal; REB 2023-561) [36], Ottawa (Royal Ottawa Health Care Group; REB 2022034) [37], Kingston (Kingston Health Sciences Center; REB 6037321) [38], Toronto (Ontario Shores Centre for Mental Health Sciences; REB 38116) [39], and Vancouver (Vancouver Coastal Health; REB H22-02300) [40]. The research adheres to the principles outlined in the Tri-Council Policy Statement: Ethical Conduct for Research Involving Humans and complies with Canadian legal requirements for scientific research involving human participants, including the Privacy Act and applicable clinical trial regulations [41]. Participants provide informed consent through a comprehensive process that includes a detailed explanation of the study’s objectives, procedures, potential risks and benefits, and their rights as research participants, in accordance with the Tri-Council Policy Statement: Ethical Conduct for Research Involving Humans guidelines. This process will involve both written documentation and verbal discussion, and participants will be informed of their right to withdraw from the study at any time without consequence to their ongoing care. Particular attention will be given to ensure an understanding of these processes among individuals with SSDs. All collected data will be deidentified using unique participant codes, with personal identifiers stored separately in encrypted files accessible only to authorized research personnel. In terms of compensation, participants will receive monetary remuneration for each completed assessment measure, with a standardized gift card amount of US $18 per assessment session or focus group. This compensation structure ensures fair and consistent reimbursement for participants’ time and effort while maintaining ethical standards for human participant research. The compensation details will be clearly communicated to participants during the informed consent process to ensure transparency and avoid undue influence on participation decisions.

### Measures

To assess the effectiveness of the 2 digital cognitive health interventions (objective 1), primary outcomes will encompass quantitative measures of cognitive function for ABCR and cognitive biases for MCT. These outcomes were selected in alignment with the primary targets for each intervention and primary outcomes assessed in the past ABCR and MCT studies. To capture the full extent of these outcomes, both objective and self-report measures were selected. The collection of these primary outcomes will be prioritized. Secondary outcomes for both interventions will include clinical and functional measures. Propensity score matching will consider background characteristics such as sociodemographic variables, illness duration, medication dosage, length and nature of prior treatment, and subjective reports of cognitive capacity and biases. To promote data quality, research staff will partake in centralized interrater reliability sessions every 6 months. To evaluate the implementation strategy (objective 2), a combination of quantitative and qualitative data will be gathered. Refer to Table 1 for a breakdown of the data types to be collected, organized by objectives, time points, and stakeholders.

**Table 1 table1:** Summary of the type of data to be collected as a function of objectives, time points, and stakeholders.

Objectives or data type and measures			Measurement time points		Stakeholder groups
**1. Effectiveness (quantitative)**					
	Cognitive tests or tasks: Brief version of the CANTAB^a^ computerized battery (Intra-Extra Dimensional Set Shift, Stocking of Cambridge, and Spatial Working Memory)^b^ [42] Wechsler Memory Scale (Logical Memory Subscale)^b^ [43] Cognitive bias against disconfirmatory evidence story^b^ [44] Jumping to conclusions (Beads)^b^ [45] Subjective cognition: Subjective Scale to Investigate Cognition in Schizophrenia (Brief)^b^ [46] Cognitive Motivation Scaleb [47] Davos Assessment of Cognitive Biases Scale^b^ [48] Symptoms: Positive and Negative Syndrome Scale-6 [49] Brief Negative Symptom Scale [50] Psychotic Symptom Rating Scales [51] Psychosocial: Self-Esteem Rating Scale—Short Form [52] Overall Emotional and Social Loneliness Scale [53] Short Warwick-Edinburg Mental Well-Being Scale [54] Questionnaire About the Process of Recovery [55] Basic Psychological Need Satisfaction and Frustration Scale [56] Autonomous-Controlled Motivation for Intervention Questionnaire [57] Personal and Social Performance [58]	Preintervention Postintervention 3-month follow-up		Service users	
	Intervention: Health Care Climate Questionnaire [59] Autonomous-Controlled Motivation for Intervention Questionnaire [57] MMI^c^ Cognitive Training Questionnaire [60] Satisfaction With Therapy (STQ^d^) [61] Time spent on cognitive drill exercises (ABCR^e^) Last log in (iCog platform)	Midintervention		Service users	
